### Randomisation, allocation and concealment

Participants who complete baseline measures will be randomised into one of two groups: 1) HIIT or 2) 10,000 steps (Fig. 1). Each participant will be randomized into one of the two study conditions according to an allocation sequence generated by a computer program and concealed within sealed opaque sequentially numbered envelopes. Analyses will adjust for any baseline differences, consistent with standard procedures. Participants will be allocated to conditions one-at-a-time, allowing for a “rolling start” to the intervention.

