### Data collection

Participants will be assessed on three occasions: at baseline, week 13 and week 26 (see Fig. 1). Cigarettes per day will be measured weekly. Withdrawal symptoms, cigarette cravings and feelings of stress, will be monitored during the intervention. See Table 2 for full list of measures, and measurement time-points. Exercise and fitness measures will be completed by research staff whom will be blinded to participant group allocation.

**Table 2 Tab2:** Timeline for data collection

	Measurement time-point					
Measures	Baseline	Week 2	Week 4	Week 8	Week 13	Week 26
Cigarettes per day (weekly)						
Smoking cessation					X	X
Withdrawal symptoms	X	X	X	X	X	X
Cigarette cravings	X	X	X	X	X	X
Cigarette dependence	X				X	X
Subjective stress	X		X	X	X	X
Saliva cotinine	X				X	X
Cardiorespiratory fitness	X				X	X
Lung function	X				X	X
Body composition	X				X	X
Physical activity	X				X	X
Well-being	X				X	X
Motivation	X				X	X
Demographic information	X				X	X

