### Smoking measures

*Smoking abstinence and cessation* will be assessed using the Russell Standard [12]. This includes self-reported ‘quitting’ (not smoking for two weeks) and expelled carbon monoxide concentration (Micro Smokerlyser; Pico simple, Harrietsham, UK) of less than 10 ppm (which reflects abstinence from smoking during the previous 24-h). *Saliva* will be collected by drooling into a 50 ml Falcon tube. The sample will be frozen and stored for analysis of cotinine, which is a metabolite of nicotine. *Self-reported number of cigarettes* smoked will be recorded each week. *Withdrawal symptoms* and *cravings* will be assessed using the Mood and Physical Symptoms Scale (MPSS) [13]. *Smoking dependency* will be assessed using the Fagerström Test for Nicotine Dependance (FTND) [14]. *Subjective stress* will be assessed using the 4-item Perceived Stress Scale (PSS) to monitor any changes associated with smoking reduction or increasing PA [15].

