### Data analysis

The aim of this study is to obtain data on the effects of HIIT training on smoking cessation and intermediate outcomes, such as cigarette cravings and withdrawal symptoms. Using effect size estimates based on results of a previous study using vigorous PA for smoking cessation in women (i.e. OR = 2.09, [18]), adopting a two tailed alpha level of 0.05 and power 0.80, a sample size of 100 will be required. Based on funding and time constraints, the study aims to recruit 50 participants per group. Descriptive statistics will be used to summarize the characteristics of participants in each group, and to describe those who successfully quit. Yates’ corrected Chi-squared test will be used to analyse the difference in the proportions who quit in each group, and changes in categorical (e.g. smoking abstinence) and continuous (e.g. number of cigarettes smoked) variables will be assessed using generalised linear modeling.

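### Outcomes are to be analysed as changes without a firm commitment to each outcome's baseline value as covariate; the test stays valid but can lose precision

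*Protocol article*

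**What the plan says.** Two sentences in the protocol article bear on this point.

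- Data analysis fixes the target and the model class: "changes in categorical (e.g. smoking abstinence) and continuous (e.g. number of cigarettes smoked) variables will be assessed using generalised linear modeling".
- Randomisation, allocation and concealment contains the only statement on baseline: "Analyses will adjust for any baseline differences, consistent with standard procedures".

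The data come from a schedule with a baseline value and repeated follow-up.

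- Data collection states: "Participants will be assessed on three occasions: at baseline, week 13 and week 26". Table 2 shows withdrawal and cravings at baseline and five later times, stress at baseline and four later times, and dependence, fitness, body composition and most other measures at baseline and two later times.
- For cigarettes, Data collection says "Cigarettes per day will be measured weekly", and Smoking measures says that the self-reported number "smoked will be recorded each week".
- Smoking cessation has no baseline entry in Table 2, and Table 1 requires every participant to be a current smoker.

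The group comparison of quitting is separate: "Yates’ corrected Chi-squared test will be used to analyse the difference in the proportions who quit in each group".

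**The concern.** A change score subtracts the whole of the baseline value from the follow-up value. Unless the two are almost perfectly correlated, that subtracts too much and adds the noise of the baseline measurement to the outcome. Entering the baseline value as a covariate lets the data set the weight, and the residual variance falls.

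The gain does not depend on whether the groups differ at entry. It comes from the correlation between baseline and follow-up. If the group means at baseline happened to be identical, the change-score and baseline-adjusted estimates of the group difference would coincide, yet the unadjusted change score would still carry the larger standard error. A rule that adjusts when a difference is seen therefore uses the wrong trigger. It also leaves the choice of covariates to be made after the data are seen.

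At stake is precision for the intermediate outcomes that the article names in its analysis aim (cravings and withdrawal) and for weight, its second aim. The article says that recruitment of 50 per group is set by funding and time, so precision cannot easily be bought with more participants.

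**Working it through.** **Inputs.** 50 women per group (Data analysis). Baseline and follow-up values per woman (Table 2). The article gives no standard deviation and no baseline-to-follow-up correlation, so it has no figure of its own to reproduce on this point. I assume r = 0.3, 0.5 and 0.7, with a common variance of 1 at baseline and follow-up.

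**Step 1, variance per woman.**

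- Change score without baseline: 1 + 1 − 2r = 2(1 − r).
- Follow-up value adjusted for baseline: 1 − r².
- Ratio: 2(1 − r)/(1 − r²) = 2/(1 + r).

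| Assumed r | Change score, 2(1−r) | Baseline-adjusted, 1−r² | Variance ratio | SE ratio | 100 women count as 100(1+r)/2 |
|---|---|---|---|---|---|
| 0.3 | 1.40 | 0.91 | 1.54 | 1.24 | 65 |
| 0.5 | 1.00 | 0.75 | 1.33 | 1.15 | 75 |
| 0.7 | 0.60 | 0.51 | 1.18 | 1.08 | 85 |

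**Step 2, does it depend on equal variances?** With standard deviations s0 at baseline and s1 at follow-up, the change-score variance is s0² + s1² − 2r·s0·s1 and the adjusted variance is s1²(1 − r²). The difference is s0² − 2r·s0·s1 + r²·s1² = (s0 − r·s1)², which is never negative. The size of the loss varies with the variances; its direction does not.

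**Step 3, is the unadjusted test still valid?** Linear models were simulated with 50 per group, one value per woman and no group effect, 4,000 runs for each r.

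| Assumed r | Type I error, change without baseline | Type I error, change with baseline | Mean SE without | Mean SE with |
|---|---|---|---|---|
| 0.3 | 0.050 | 0.048 | 0.235 | 0.191 |
| 0.5 | 0.047 | 0.046 | 0.199 | 0.173 |
| 0.7 | 0.048 | 0.049 | 0.155 | 0.143 |

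Both tests hold the 5% level. The standard errors match the formula: at r = 0.5 it gives √(1.00 × 2/50) = 0.200 and √(0.75 × 2/50) = 0.173.

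**Step 4, does it matter whether change or follow-up is the response?** With baseline in the model, no. The simulated standard errors and rejection rates were identical for the two responses, because subtracting a covariate from the response shifts only that covariate's coefficient. The group coefficient on adjusted follow-up weight therefore still answers the aim on weight change.

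**The case against.** The best defence is that the article does mention baseline adjustment. Read generously, the Randomisation sentence means that every analysis will include the baseline value, and then nothing is lost (Step 4). Nothing in a generalised linear model prevents this. The article also condenses a fuller document, where covariate lists usually stand. Part of this holds: the article does not say that baseline will be left out. But the one sentence it offers ties adjustment to differences, names no outcome's baseline value, and stands beside a stated target of change. That stated wording can be improved; it is not mere silence.

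A reader might go further and infer that the visits will be stacked and each woman's values treated as independent, which would understate the standard errors. With all post-baseline values pooled in that way at a within-woman correlation of 0.5, type I error would be about 11% with two visits and 26% with five. The article does not support this inference. It does not say that visits are pooled, does not give the unit of analysis, and does not exclude a mixed model or generalised estimating equations. Its target of change fits one value per woman at least as well, and that analysis is valid. The choice of correlation structure is commonly left to the full plan, so those figures describe an analysis the article never states.

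A reader might also call change in abstinence an empty outcome. Since all women smoke at entry, abstinence at follow-up is itself the change, and movement between weeks 13 and 26 is meaningful. That is a matter of wording only.

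**Conclusion.** The point holds as a loss of precision that is free to avoid, not as an error in inference. If change scores are analysed without the outcome's baseline value, variance is 54%, 33% or 18% higher than need be at assumed correlations of 0.3, 0.5 or 0.7, which makes standard errors 24%, 15% or 8% larger. If baseline is always a covariate, the loss is nil.

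The figures rest on assumed correlations, equal variances at baseline and follow-up, and a linear model with one value per woman. For cigarette counts under another link they are only a guide. The documents do not show that standard errors will be wrong or that false positive findings will follow. The Yates-corrected quit comparison uses one value per woman and is untouched.

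**What to change.** Replace the clause on changes, and the Randomisation sentence on baseline differences, with wording to this effect:

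> For each outcome measured at baseline (cravings, withdrawal, dependence, stress, fitness, weight and the like, and cigarettes per day using the count at entry), the follow-up value will be modelled with group and that outcome's baseline value as covariates. The baseline value will be included whether or not the groups differ at baseline. Where several visits enter one model, a mixed model or generalised estimating equations will allow for correlation within participant. Abstinence will be modelled as status at week 13 and at week 26.

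The third sentence is a clarification, not a correction. The change costs a few lines of analysis wording and one covariate per model. It needs no new visits, participants or measurements, provided the entry cigarette count is kept as a number. It should be settled before outcome data are compared by group.

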## Discussion

Physical inactivity and tobacco smoking are important contributors to the overall burden of disease in Australia, and are significant risk factors for almost all Australia’s major non-communicable physical and mental health problems.

This study is innovative, as it will build on suggestions from previous studies that intensity of exercise may be a critical factor in determining the efficacy of PA interventions for smoking cessation. Our study addresses this issue by comparing the effect of two PA interventions of varying intensity on smoking cessation outcomes.

In examining the notion that HIIT (combined with a quit program) will result in higher quit rates than a more moderate PA intervention, we will also examine novel mediators (fitness, vitality and intrinsic motivation) which will improve understanding of the relationships between HIIT and smoking cessation.

Further, we will assess the effect of exercise intensity on other indicators of smoking, such as withdrawal symptoms, cigarette cravings and weight gain, as these factors are important barriers to smoking cessation. This project will address the weaknesses of previous studies (e.g. poor assessment of intensity, adherence or compliance to exercise) and is novel in design and conceptualisation.

HIIT has potential to impact on individual cardiovascular health and to be a very cost effective intervention, compared with other cardiovascular treatments (e.g. statins), as it may address two major contributors to cardiovascular disease (smoking and physical inactivity) in one intervention. The research will inform efforts to develop novel, innovative, and time efficient strategies for promoting cardiovascular health in women.

## Abbreviations

BREQ: Behavioural Regulation in Exercise Questionnaire
FTND: Fagerström Test for Nicotine Dependance
HIIT: high intensity interval training
HRmax: heart rate maximum
MPSS: Mood and Physical Symptoms Scale
PA: physical activity
PICF: participant information and consent form
PSS: Perceived Stress Scale
VO_2_max: maximal oxygen uptake
